### Study design and hypotheses

2.1

This three-arm, non-randomized controlled trial investigates the efficacy of Ayahuasca-assisted Meaning Reconstruction therapy (A-MR) in decreasing normal and pathological grief symptoms in people who have lost a first-degree relative within the prior 12 months. Participants are sequentially allocated to the following treatment conditions: (1) a control group receiving Meaning Reconstruction therapy (MR), (2) a control group receiving No Treatment (NT), and (3) an experimental group receiving Ayahuasca-assisted Meaning Reconstruction therapy (A-MR).

The objective of this trial is two-fold. First, our aim is to compare the efficacy of A-MR with that of MR and NT by assessing differences in (a) the severity of normal grief symptoms, (b) pathological grief symptoms, (c) quality of life, and (d) posttraumatic growth. Moreover, we are also interested in analyzing how each condition may influence the proposed processes of change: (e) meaning-made (f) psychological flexibility, and (g) self-belief consistency. Additionally, we will explore the participants’ (h) subjective effects of ayahuasca and the (i) acceptance-avoidance promoting effects.

The following hypothesis will be tested:

Hypothesis 1. The experimental group receiving A-MR will show greater improvement in normal and pathological grief symptoms, quality of life, and post-traumatic growth compared to both control groups (MR and NT), at post-treatment and 3 months follow-up. Moreover, MR group will show greater improvement than the NT group, expecting a medium clinical effect size.

Hypothesis 1.1. The experimental group receiving A-MR will show greater improvement in psychological flexibility, meaning-made, and self-believed consistency compared to both control groups (MR and NT), at post-treatment and 3 months follow-up. Furthermore, MR will also show greater improvement than the NT group, expecting a medium clinical effect size.

Hypothesis 2. Reductions in the severity of normal and pathological grief symptoms will be principally related to changes in meaning- made, but also to changes in psychological flexibility and self-belief consistency. Moreover, a stronger relationship between changes in the severity of grief symptoms and meaning-made is expected in the A-MR group.

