### Procedure

2.3

Participants will be recruited through the newsletter, webpage, and social media accounts of the Beckley Foundation, Beckley Med, MIND Foundation and the International Center for Ethnobotanical Education, Research and Service (ICEERS), all of them European institutions dedicated to psychedelic research and education. Upon receiving the request to participate in the trial, the participant will be prompted to complete a short online questionnaire to screen for inclusion criteria. Those who meet the inclusion criteria will attend a video-call interview with the principal investigator (DG) to learn more about what their participation would entail and to screen whether any exclusion criteria are met. They will also be informed about the need to verify their blood pressure range with a general practitioner to prevent potential ineligibility, given that blood pressure measurement is taken on-site before each ayahuasca session. Then, those who are eligible will provide informed consent. Assessments will be conducted online at baseline (T0), during treatment (T1 and T2), at post-intervention (T3), and at 3-month follow-up (T4) (see **Figure 1**).

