### Data analyses

2.6

All the studied variables will be descriptively analyzed by means (SDs), medians (ranges) or n (percentages). Between groups baseline differences will be tested using 2-tailed t-test, Man-Whitney test or chi-square/Fisher’s exacts test based on the type of variables compared.

Despite the trial being exploratory study, data will be analyzed following the intent-to-treat and/or completer strategies, based on the presence of drop-out. The first hypothesis (H1) will be tested using an independent two-way repeated measures analysis of variance (ANOVA) with 3 levels for each factor (Group: A-MR *vs* MR *vs* NT; Time: pre-treatment *vs* post-treatment *vs* follow-up) and/or Linear Mixed Models (LMM) for each primary and secondary outcome studied. The LMM will be used to analyze the possible effect of between groups differences at baseline measures as covariables, and to analyze the effect of the presence PGD diagnoses following the ICD-11 duration criterion at baseline. Bonferroni corrections will be applied to all analyses, and partial eta-square and Cohen’s *d* effect sizes will be calculated for interaction effects and for between- and within-group comparisons, respectively. Confidence intervals for Cohen’s *d* will be estimated at a 95% confidence level and 500 bootstrap samples.

The analysis of the second hypothesis (H2) will be based on the outcomes of testing H1, with reduction in grief severity (TRIG and TGI scores) as the dependent variable for mediation analyses. The mediation model will include all participants in the study and will only incorporate the potentially significant mediating variables (meaning-made, psychological flexibility, and self-belief consistency) identified in previous analyses. Power analyses for the mediation models will also be conducted based on a Monte Carlo simulation.

The statistical analyses will be conducted using R version 4.2.3 (79). The following R packages will be used for data exploration, description, and preprocessing if necessary: tidyverse (80), car (81), moments version 0.14.1 (82), and nortest version 1.0-4 (83). The repeated measures ANOVAs and/or Lineal Mixed Models will be conducted using rstatix package version 0.7.2 (84). Finally, the mediation model will be tested using the lavaan package version 0.6-12 (85) and statistical power for the mediational analysis will be calculated using WebPower package version 0.9.4 (86).

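### The H2 mediation model screens the named mediators on earlier results, so meaning-made, or a mediator it must be ranked against, can be dropped before H2 is tested

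*Protocol article*

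**What the plan says.** All references are to the protocol article.

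- **Study design and hypotheses (2.1).** H2 has two sentences. The first ranks meaning-made as the principal correlate of grief reduction, "but also to changes in psychological flexibility and self-belief consistency". The second says that "a stronger relationship between changes in the severity of grief symptoms and meaning-made is expected in the A-MR group".
- **Data analyses (2.6).** The section opens this topic by stating that "The analysis of the second hypothesis (H2) will be based on the outcomes of testing H1". The outcome of the model is the fall in the two grief scores, TRIG and TGI. On population, "The mediation model will include all participants in the study". On content, the model "will only incorporate the potentially significant mediating variables (meaning-made, psychological flexibility, and self-belief consistency) identified in previous analyses". The section gives no threshold for this screen, no interval for the change scores and no term that lets the meaning–grief relationship differ by arm.
- **Table 1.** The three mediator scales (ISLES-SF, AAQ-II, SCS) are scheduled at T0, T3 and T4, the same visits as the analysed TRIG and TGI-SR scores. T1 and T2 carry only the two acute-experience scales.

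**The concern.** The screen is a stated rule and not a gap in a condensed article. A fuller plan could repair it only by reversing it. It has three consequences.

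1. **It asks a different question.** The group tests (H1.1) ask whether arms differ on a mediator. H2 asks whether change in a mediator goes with change in grief. A mediator can track grief closely while the arm difference misses significance in a small trial.
2. **It can remove what H2 compares.** Ranking meaning-made first requires meaning-made and its two comparators in the same model.
3. **The screen is loosely defined.** The ANOVA or mixed model is described for primary and secondary outcomes, whereas the mediators are listed in a separate section (2.5.3). It is therefore unclear which earlier analyses and which significance level decide entry.

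The Discussion says a later trial would prioritise mechanisms identified by these mediation analyses. A mechanism discarded untested would drop out of that programme. Separately, the second sentence of H2 is a prediction with no analysis described for it.

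**Working it through.** **The plan's own figure.** No sample size is given for mediation. The 69 was set for TRIG change, A-MR against NT, with d = 0.84, correlation 0.55, power 0.90 and alpha 0.05 (Sample size, 2.4). It is reproduced by a one-sided two-sample t test on change scores: 0.84/√(2 × (1 − 0.55)) = 0.885, which needs 23 per arm, and 3 × 23 = 69. The sidedness is my inference, since the article does not state it.

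**Inputs for the screen.** n = 23 per arm and r = 0.55 come from the article; applying r to the mediator scales is my assumption. H1.1 expects a medium effect for MR against NT, which I take as d = 0.5. The significance level is not stated, so I use 0.05 and 0.05/3 (three mediators).

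**Case A: two-arm comparison, d = 0.5.**
- Post scores: noncentrality = d√(n/2) = 0.5 × √11.5 = 1.70 on 44 df.
- Baseline-adjusted: d/√(1 − r²) = 0.5/√0.6975 = 0.599, so noncentrality = 0.599 × √11.5 = 2.03 on 43 df.

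**Case B: three-arm omnibus F test, arm means 0/0.5/1.0 (A-MR as far above MR as MR is above NT).**
- Post scores: noncentrality = 69 × variance of the means = 69 × 0.1667 = 11.5 on 2 and 66 df.
- Baseline-adjusted: 11.5/0.6975 = 16.5 on 2 and 65 df.

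| Screen | Pass at 0.05 | Fail at 0.05 | Pass at 0.05/3 | Fail at 0.05/3 |
|---|---|---|---|---|
| A, post scores | 0.38 | 62% | 0.23 | 77% |
| A, adjusted | 0.51 | 49% | 0.33 | 67% |
| B, post scores | 0.85 | 15% | 0.72 | 28% |
| B, adjusted | 0.95 | 5% | 0.89 | 11% |

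Mediators that do pass look stronger than they are. In case A on post scores at 0.05, the mean estimated difference among those that pass is 0.78 against a true 0.50 (20,000 simulated comparisons).

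**Second sentence of H2.** Compare the within-arm correlation in A-MR (n = 23) with that in the other two arms together (n = 46), using Fisher's z. The standard error is √(1/20 + 1/43) = 0.271. Two-sided 5% power is Φ(difference in z/0.271 − 1.96). For 0.5 against 0.3 this is 14%, for 0.6 against 0.3 it is 29%, and for 0.7 against 0.3 it is 54%.

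**Direction of effect.** I simulated 3 × 23 participants with an arm effect on grief of 0.84 SD and meaning change generated only from grief change (correlation about 0.6 within arm). A same-interval model declared mediation in about 39% of trials, although meaning caused nothing. The opposite case was also simulated: meaning change drives the T0–T3 grief reduction and has no further effect. A lagged model (T4 grief, adjusted for T0 and T3 grief) then found mediation in about 4% of trials, against about 80–92% for the same-interval model, depending on the assumed path strengths.

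**The case against.** Several arguments on the other side have force.

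- **The loss rate may be modest.** The medium effect in H1.1 refers to MR against NT, and A-MR is expected to do better than MR. The stated H1 method has three groups. Under case B the screen usually passes a real mediator. This stands: the 49–77% failure range belongs to case A alone and is not a general rate. It does not rescue the rule, which still selects on the wrong question.
- **A reader might infer that the plan cannot test H2 at all.** The documents do not support that. H2 is worded as a relationship between changes, and same-interval change scores address that wording directly. What they cannot do is show direction.
- **A reader might infer that the plan commits to same-interval change.** It does not. No interval is fixed, T3 and T4 are both planned, and a lagged model is not excluded. Such detail may sit in a fuller plan.
- **A reader might infer that pooling the arms is itself a fault.** It is not. Mediation of an arm effect needs all arms, and an all-participant model can hold an arm by mediator term or be fitted as a multi-group model. The supportable point is narrower: no analysis is described for the second sentence of H2.
- **The trial is called exploratory.** True, and this lowers the stakes. But an exploratory study of mechanisms has more reason, not less, to report all the mechanisms it named.

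**Conclusion.** The concern holds for the screening rule. As written, the test of H2's first sentence is conditional on earlier results that answer another question, and the principal mediator or a comparator can be removed before the ranking is examined. The chance of losing a real mediator runs from about 5% (omnibus, means 0/0.5/1.0, baseline-adjusted, 0.05) to about 77% (two-arm, d = 0.5, post scores, 0.05/3). All of these rest on assumed effect sizes and an assumed threshold. The second sentence of H2 lacks a described analysis, and with 23 in A-MR any test of it would have low power. Timing is a matter of interpretation: same-interval models support association only, and the lagged model addresses later change, a different estimand and not merely a less powerful version of the same one.

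**What to change.** 1. Delete the screening rule. Enter meaning-made, psychological flexibility and self-belief consistency together, whatever their earlier group-test results, with arm in the model.
2. For the second sentence of H2, add an arm by meaning-made term or fit a multi-group model. Report the difference with a confidence interval and do not judge it by a significance test.
3. State the interval for each change score, and describe same-interval results as associations that do not establish direction.
4. Optionally add a lagged sensitivity analysis: mediator change T0–T3, with grief at T4 adjusted for arm and for grief at T0 and T3. Keep it beside the same-interval model, because it misses mediation that occurs during treatment.

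The cost is a few lines of text, more terms in a model with N = 69, and wider intervals. No new visits or measures are needed.

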### Intervention

2.7

#### Meaning Reconstruction therapy

2.7.1

The psychotherapy protocol, part of both the A-MR and the MR group, is grounded in a meaning reconstruction approach to grief therapy (37, 38, 87). This model focuses on the crucial role of meaning-making in recovery and posttraumatic growth after the death of a significant person (69, 88–90). The intervention follows a tripartite approach that helps mourners overcome obstacles in making sense of the loss, reworking their attachment relationship to the deceased, and reconstructing their identities in light of the experience (37, 38). Open trials of the model with both unselected self-referred groups experiencing loss and transition (91) and mourners meeting criterial for PGD (92) have strongly supported the effectiveness of the model and, added to a growing literature, indicate that meaning-making prospectively predicts positive adaptation to bereavement (88, 92–95).

The 9-session A-MR and MR can be subdivided into the three domains defined in meaning reconstruction theory: the “event story” of the loss, the “back story” of the relationship with the deceased, and the “personal story” of self (37, 38) (**Table 2**):

The first phase is focused on the employment of non-directive narrative retelling to help the participant revisit the story of the loss, and the stressful or traumatic memories connected to it (37, 96, 97). This technique, when conducted in a safe and low-avoidance setting, can enable the bereaved to reconstruct a coherent narrative of the loss and its implications through introspection and deliberative processing and integration of its meaning. When necessary (e.g. when significant anxiety is present), relaxation and/or mindfulness techniques are introduced to manage activation and foster self-regulation.The second phase is focused on promoting a secure attachment with the deceased (98), addressing unfinished business, or processing anger and guilt (37). Different techniques are employed to help reconstruct the internal representation of the deceased, such as introducing the deceased (99) and engaging in an imaginal conversation with them (100). When appropriate, and desired by the participant, a key aim is to establish and maintain a constructive continuing bond with the deceased (101).The third and last phase prioritizes the reconstruction of the bereaved person’s sense of self and their future as a survivor (7, 102). The Bull’s-Eye Values Survey (BEVS), a contextual form of behavioral activation and values clarification, is employed to restore the participant’s life orientation without the deceased (103).

Participants will complete a 50-minute session on a weekly basis, conducted online through a secure videoconference platform in compliance with HIPAA guidelines. Every therapist in the trial is a licensed psychologist, and all of them have received specialized training in the delivery of the treatment protocol. Furthermore, they have access to clinical supervision provided by DG and PS upon request. All the therapists have prior experience in PAP and/or psychedelic integration and are affiliated with the Spanish Society of Psychedelic Medicine (SEMPSi).

#### Ayahuasca-assisted Meaning Reconstruction therapy

2.7.2

The experimental group intervention (A-MR) adheres to the same online Meaning Reconstruction Therapy protocol, with the incorporation of up to two onsite ayahuasca sessions following phase 1 (session 3) and phase 2 (session 6) (see **Table 2**). The first ayahuasca session is preceded by a preparatory online group session (after session 1) and is followed by an online individual integration session during the week after the ayahuasca administration. This design is based on the contemporary structure of PAP, which typically involves a three-stage framework encompassing preparation, facilitation, and integration (104).

**Table 2 T2:** Ayahuasca-assisted meaning reconstruction protocol (A-MR).

Phases	Psychological content	Session	Techniques
Opening	Fostering therapeutic alliance; Exploring potential difficulties; Psychoeducation: Dual model of grief coping	1	
On-line preparation of ayahuasca session*			
**Phase 1:** The “event story” of the loss	Processing traumatic or stressing memories, and finding meaning in loss and in life	2	Narrative retelling
		3	Narrative retelling
First ayahuasca session*			
Integration of ayahuasca experience*			
**Phase 2:** The “back story” of the relationship with the deceased	Restoring attachment security through reconstructing a bond with the deceased and/or processing unfinished business	4	Introducing the deceased
		5	Imaginal conversation with the deceased
		6	Internal representation of the deceased’s reconstruction
Second ayahuasca session*			
Integration of ayahuasca experience*			
**Phase 3:** The “personal story” of self	Reorganizing one’s identity and life orientation as a survivor	7	Bull’s-Eye Values Survey
		8	Bull’s-Eye Values Survey
Ending	Summary of the psychotherapeutic process	9	

*Excluded in the MR intervention protocol.

The objective of the preparation session is for participants to become familiarized with one another, address any uncertainties that might arise after reviewing the written information provided, and foster an appropriate expectation for the upcoming ayahuasca experience. Psychedelic integration following the ayahuasca session is conducted in alignment with the non-directive principles of restorative retelling (100, 105). Restorative retelling facilitates the assimilation of the phenomenology of the ayahuasca experience, while helping the person reconstruct their schemas and narratives about themselves, other people and the world, through a process of accommodation. A detailed outline of this method of psychedelic integration has been published elsewhere, in the form of a case study (106). Features of the psychedelic experiences that persist, or could gradually unfold, are further addressed during the remaining psychotherapeutic process.

##### Ayahuasca session procedure

2.7.2.1

Each ayahuasca session is conducted onsite over a 24-hour period, starting on Saturday morning. At 11:00 am, each participant is asked to attend an initial group meeting to discuss how the day will be organized. Immediately after that meeting, blood pressure and body weight are assessed by a medical doctor to ensure that this inclusion criterion is met, and to calculate the appropriate ayahuasca dose for each participant.

At 13:00h, a second meeting takes place to practice mindfulness exercises in a group format, which are aimed at promoting a low-avoidance and present-focused mindset during the psychedelic experience. Before the start of the first ayahuasca session at 14:30h, each participant takes part in a one-hour group dynamic during which they introduce their loved one to the rest of group, by sharing photos of the deceased (99). During the second ayahuasca session, this activity is replaced by an art-therapy activity, the dual rose technique, which can aid in the reconstruction of meaningful memories of the deceased and the relationship with them (107). Both activities help anchor the psychological content related to the loss in the participants’ mindset, immediately before the ayahuasca administration takes place.

During the ayahuasca session in the afternoon, participants recline on a comfortable couch in a quiet, ample room, while listening to the same instrumental music through a loudspeaker. They are encouraged to focus their attention inward, and research staff are always present in the room to address participants’ needs. Psychedelic effects typically last 5 hours, approximately, and participants are encouraged to describe their experience in writing during the 2 hours immediately afterward. Those who prefer to paint or draw to assimilate and express their experiences, instead of writing them down, are provided with the materials to do so.

After this period of rest and reflection, a healthy vegetarian dinner is provided. Subsequently, participants sleep under medical supervision. The following morning, a light breakfast is served. Participants are then invited to optionally share their ayahuasca experiences in a group setting, expressing themselves as they feel comfortable. During this sharing, non-directive principles are followed to validate their psychedelic experiences. Before the session is over, they are provided with general information and advice regarding the sensitive state they may find themselves afterward, and how to manage it.

Ayahuasca sessions will be conducted in groups of up to eight participants, supported by a team of four facilitators. The primary responsibility of the facilitators is to ensure the physical and psychological safety and trust of participants throughout the session. They also provide non-directive support to help participants engage openly with their internal experiences as they emerge. The facilitator team includes the head of the Santo Daime Church (Barcelona), a psychiatrist (JJ), a nurse, and the principal investigator of the study (DG). All facilitators have extensive experience supporting individuals through altered states of consciousness. Their expertise spans religious settings, clinics treating treatment-resistant depression with ketamine-assisted psychotherapy, and several psychedelic research studies. They have also collaborated with retreat centers administering ayahuasca and psilocybin, in both traditional and non-traditional contexts.

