**Method:**

The outlined protocol is a three-arm, non-randomized controlled trial focused on reducing normal and pathological grief symptoms, comparing the effectiveness of Ayahuasca-assisted MR therapy (A-MR), MR therapy alone (MR) and No Treatment (NT). At least 69 people who lost a first-degree relative during the prior year, and with a Texas Revised Inventory of Grief score up 39 (TRIG ≥ 40), will participate in the trial. Participants will be allocated to an A-MR (n ≥ 23), MR (n ≥ 23) or NT (n ≥ 23) group. Those from the A-MR and MR therapy groups will undergo a therapeutic process involving 9 sessions of online psychotherapy. In addition, the A-MR condition involves 2 group sessions of ayahuasca. The primary outcomes will be normal and pathological grief severity as measured by the TRIG and Traumatic Grief Inventory Self-Report (TGI-SR), administered at baseline, post-treatment, and 3-month follow up. Measures of quality of life, post-traumatic growth, meaning-made, psychological flexibility, and self-belief consistency will be also included. In addition, subjective effects of ayahuasca and acceptance-avoidance promoting effects will be assessed following ayahuasca administration. Finally, we will analyze the potential mediating effect of meaning-made, psychological flexibility and self-belief consistency in grief symptoms (as measured by the TRIG and TGI).

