### Sample size

2.4

Given that no comparative trials analyzing the therapeutic effect of PAP on reduction of grief symptoms has been published to date, sample size was calculated based on the results of González et al. (35) observational study. The observed Cohen’s d (0.84) for the study group between the baseline and the 15^th^-day-post-treatment assessment, and TRIG measurement correlation of 0.55, were used to estimate the sample size for this study. Therefore, sample size was calculated based on the assumption of a between groups differences at post-treatment of at least 9.4 points (TRIG score) in mean change between the A-MR and the NT groups. Sample size with power of 0.90 and an alpha of 0.05 was calculated using pwrss R package version 0.3.1 (58). To find at least the above effect size, a total sample of 69 participants is needed, but as drop-out rate of 20% were considered, 84 participants will be recruited.

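### Only the A-MR arm is treated in groups, and the planned Group x Time ANOVA and the sample size ignore this. If outcomes correlate within session groups, the standard errors of the A-MR contrasts are understated

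*Protocol article*

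**What the plan says.** **Delivery.** Section 2.7.2.1 of the protocol article states: "Ayahuasca sessions will be conducted in groups of up to eight participants, supported by a team of four facilitators". Sections 2.7.2 and 2.7.2.1 add an online preparation session held as a group, group mindfulness practice, a group activity before each dosing session, and one room with the same music. For the next morning the article says: "Participants are then invited to optionally share their ayahuasca experiences in a group setting". Integration afterwards is individual. MR is described as weekly online sessions with no group element, and NT receives nothing. Under section 2.3, controls may take ayahuasca only after the follow-up assessment, so this does not group their trial outcomes.

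**Analysis.** Section 2.6 tests the first hypothesis with an "independent two-way repeated measures analysis of variance (ANOVA) with 3 levels for each factor", the factors being Group and Time, and/or with LMMs. The stated uses of the LMM are adjustment for baseline differences and the effect of a PGD diagnosis at baseline. Session group is not mentioned, and the LMM's random effects are not described.

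**Size.** The abstract says: "Participants will be allocated to an A-MR (n ≥ 23), MR (n ≥ 23) or NT (n ≥ 23) group". Section 2.4 says: "Sample size with power of 0.90 and an alpha of 0.05 was calculated using pwrss R package version 0.3.1", and concludes that "a total sample of 69 participants is needed, but as drop-out rate of 20% were considered, 84 participants will be recruited". No ICC or design effect appears there.

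**The concern.** Participants who prepare together, share a 24-hour stay and are dosed in the same room may end up more alike than participants from different weekends. The article's own rationale makes this plausible: the Introduction describes the psychedelic state as strongly dependent on context, and context is what a session group shares. If outcomes do correlate within groups, 23 A-MR participants carry less information than 23 independent people, whereas the control arms lose nothing on this account.

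The two contrasts at the centre of the first hypothesis, A-MR vs MR and A-MR vs NT, would then have intervals that are too narrow and an error rate above nominal. In a group of eight, one unusual weekend could move 8/23 = 35% of the arm. The planned Bonferroni correction deals with the number of tests and does not repair a standard error that is too small. MR vs NT does not involve ayahuasca groups and is outside this point.

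**Working it through.** **Step 1. Reproduce the plan's sample size.** Inputs from section 2.4: a standardised effect of "d (0.84) for the study group between the baseline" and the later assessment; a correlation of 0.55; a target stated as "between groups differences at post-treatment of at least 9.4 points (TRIG score) in mean change between the A-MR and the NT groups"; power 0.90 and alpha 0.05.

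- Implied SD: 9.4 / 0.84 = 11.19.
- SD of change: 11.19 x sqrt(2 x (1 - 0.55)) = 10.62.
- Standardised difference in change: 9.4 / 10.62 = 0.885.
- Two-sample t-test, one-sided 5%: 23 per arm, power 0.905, and 3 x 23 = 69.

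The article does not state sidedness. Two-sided versions give 28 per arm (change score) or 22 (adjusted for baseline). So the one-sided change-score calculation matches the figure but is not proven to be the one used. It assumes independent participants and leaves no margin for clustering.

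**Step 2. Number of groups.** With a maximum of eight per group, 23 participants need at least 3 groups (23/8 = 2.9). If the 84 recruits split equally, 84/3 = 28 need at least 4 (28/8 = 3.5).

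**Step 3. Standard error.** Take groups of 8, 8 and 7 with the same members at both sessions.

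- Weighted group size: (64 + 64 + 49) / 23 = 7.70.
- Design effect in A-MR only: DEFF = 1 + (7.70 - 1) x ICC.
- True over naive SE, against an equal-sized arm without groups: sqrt((DEFF + 1) / 2).
- At ICC 0.05: DEFF = 1 + 6.70 x 0.05 = 1.33, and the ratio is sqrt(2.33 / 2) = 1.08.

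The type I error is for an ordinary two-sided 5% t-test, from 40,000 simulated null trials per setting. The power column uses the one-sided basis of step 1 with the correct SE and a normal approximation, which gives 0.913 at ICC 0 where the t calculation gives 0.905. It ignores the loss of degrees of freedom from having few groups.

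| Assumed ICC | DEFF | True / naive SE | Effective A-MR n | Type I error | Power |
|---|---|---|---|---|---|
| 0 | 1.00 | 1.00 | 23 | 0.051 | 0.913 |
| 0.02 | 1.13 | 1.03 | 20.3 | 0.059 | 0.897 |
| 0.05 | 1.33 | 1.08 | 17.2 | 0.069 | 0.872 |
| 0.10 | 1.67 | 1.15 | 13.8 | 0.091 | 0.830 |
| 0.20 | 2.34 | 1.29 | 9.8 | 0.132 | 0.751 |

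**Step 4. Other layouts.** With 28 in four groups of seven, the SE ratio is 1.03, 1.07, 1.14 and 1.27 at ICC 0.02, 0.05, 0.10 and 0.20, and the simulated type I error is 0.058, 0.067, 0.084 and 0.123. With groups of four, the ratio is sqrt((1.15 + 1)/2) = 1.04 at ICC 0.05 and sqrt((1.30 + 1)/2) = 1.07 at ICC 0.10.

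**The case against.** The strongest reply is that the harm is conditional and the article is a condensed document. Several parts of this stand.

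- **The ICC is unknown and may be low.** Outcomes are self-reported after nine therapy sessions and individual integration, and one facilitator team is described for all sessions. A reader might infer that every A-MR standard error is certainly understated. The documents do not support that: at ICC 0 nothing is wrong, and at 0.02 the effect is about 3%.
- **The LMM may be specified properly elsewhere.** A reader might infer that both planned models assume independence. Only the ANOVA fixes this. Random effects are commonly set in an analysis plan, and none is shown. Nor does the word independent in the ANOVA description help, since it most naturally means a separate analysis for each outcome.
- **Three or four groups is a minimum.** The limit of eight is a maximum. Smaller and more numerous groups are allowed and reduce the effect. Participants attend up to two sessions, and the article does not say whether the members are the same each time. The 8/8/7 layout is therefore close to the least favourable case.
- **The trial is exploratory and non-randomised**, and the Discussion already concedes possible bias from sequential allocation. That limits what any correction of the standard error can achieve.

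These arguments do not remove the point. The and/or wording allows the ANOVA to be the sole test of the first hypothesis, and that model has no place for session group. An exploratory trial that plans hypothesis tests, Bonferroni correction and 95% intervals still needs standard errors that suit its design.

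**Conclusion.** The point holds in conditional form. The A-MR arm is partially nested, the ANOVA treats its participants as independent, and the sample size has no allowance for clustering. If outcomes correlate within session groups, the standard errors of A-MR vs MR and A-MR vs NT are too small.

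For the 8/8/7 layout the effect is minor at an ICC of 0.02 and becomes material from about 0.05, where the true SE is 8% larger and the type I error about 7%. At 0.10 the figures are 15% and about 9%. These results rest on an assumed ICC, near-maximal group sizes, stable membership across both sessions, and no clustering in the control arms. This is a cheap improvement to the analysis, not a demonstrated error in a result.

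**What to change.** 1. Record a session-group ID for each ayahuasca session separately, since stable membership is not stated.
2. State that A-MR contrasts will not rest on the plain ANOVA alone, and report them from the LMM.
3. Prespecify a sensitivity analysis that inflates the SE of A-MR vs MR and A-MR vs NT over fixed ICCs, for example 0.02, 0.05 and 0.10, using the group sizes actually observed.
4. Add a random session-group effect in the A-MR arm only as a supportive analysis. Three or four groups estimate that variance poorly, and the estimate may be zero, so it should not carry the conclusion.

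The cost is one ID per session and a few lines of analysis text, with no extra participants. The downside is wider intervals and lower effective power for the A-MR contrasts: on the basis of step 1, from 0.913 to 0.872 at ICC 0.05 and to 0.830 at ICC 0.10.
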